## Abstract

**Background:**

Use and access to sexual and reproductive health (SRH) services are often inadequate and limited among adolescent girls and young refugee women in humanitarian settings. This is attributed to an array of factors including: limited health literacy, lack of knowledge on where and how to access services, limited availability of services, and gender norms. Further, the nature of humanitarian settings often poses additional mental health pressures because of limited safety, political instability, gender-based violence (GBV), and dire socio-economic and living conditions, among others. This is especially true for the Eastern Mediterranean Region (EMR), which hosts the largest number of humanitarian crises in the world, thus rendering the provision of SRH and psychosocial support (PSS) services in humanitarian settings highly compromised.

**Method:**

The proposed research aims to evaluate the impact of a WHO-developed low-intensity/low-resource psychosocial support (PSS) SRH-integrated intervention package on the use of selected SRH services, primarily family planning as well as well-being among Syrian adolescent girls and young women refugees, aged 15–24 years, in Lebanon. The research will adopt a community-based randomized controlled trial (RCT) design to evaluate the effectiveness of the PSS-SRH integrated intervention package on the use of selected SRH services as well as mental well-being. The RCT will be accompanied by a rigorous process evaluation during intervention implementation to assess intervention fidelity, attrition, dose and satisfaction, as well as to capture key lessons based on intervention implementation to inform global scale-up in different humanitarian settings.

**Discussion:**

This intervention is expected to be easily integrated into existing primary healthcare settings and specifically to improve selected SRH service use, leading to improved SRH outcomes and reduced SRH-related risks, and ultimately better wellbeing among refugee women and girls. Findings of this RCT are also expected to inform key stakeholders and better guide decision making for such interventions in humanitarian settings.

**Clinical Trial Registration**: https://clinicaltrials.gov/study/NCT07008950?term=self%20efficacy%20and%20knowledge&viewType=Card&rank=2, identifier: NCT07008950.

## Background

The Syrian crisis is considered one of the worst humanitarian emergencies in modern history (1). Since 2011, the crisis has led to over 13.4 million Syrian refugees in need for humanitarian assistance; more than 5.6 million of these refugees are hosted in countries near Syria, half of whom are women and girls of reproductive age (2). UNHCR estimates that over 1.5 million people from Syria currently reside in Lebanon, with only approximately 839,086 of them being UN-registered refugees. The remaining are unregistered individuals who are unable to return to Syria. Syrian refugees now amount to almost a quarter of the resident national Lebanese population, making Lebanon a country with the largest number of refugees per capita worldwide (3). Twelve years into this protracted crisis, Lebanon continues to struggle to keep pace, with no signs of any upcoming relief (3). This crisis has resulted in major public health challenges in Lebanon, including a significant strain on Sexual Reproductive Health (SRH) and mental health services for host communities and Syrian refugees (4). In addition to this crisis, Lebanon has been facing a compounded socioeconomic (Inform severity 3.6) and health crisis since 2019 (3), affecting all its resident population, including Lebanese citizens, refugees, and migrants, among others, with a disproportionate impact on the most vulnerable communities.

SRH problems are a leading cause of morbidity and mortality among girls and young women globally. During conflict or humanitarian emergencies, SRH knowledge and service use are often compromised and further compounded by increased SRH needs, violence, breakdown in health infrastructure, mental health difficulties and other vulnerabilities (5–8).

Evidence in Lebanon indicates an increased risk of sexual and gender-based violence (GBV), reproductive tract infections (RTIs), and pregnancy complications among Syrian refugee women (9, 10), all of which have been associated with increased morbidity and mortality (11). Rates of GBV are reported to exceed 30% among Syrian refugees (7–10) which further interferes with women's mobility and SRH choices and decisions (12). Access to family planning, which is critical for preventing unwanted pregnancies, unsafe abortion, and reducing maternal and child mortality, is reported to have decreased to 34.5% among Syrian women refugees living in Lebanon compared to 58.3% in Syria before the war (10). The same pattern is also observed for access to antenatal care. According to a study among Syrian refugees in Lebanon, a significant proportion of Syrian refugee women (up to 82.9%) reported only one antenatal visit while very few (only 15.7%) reported having four or more visits (13). A high prevalence of reproductive morbidities has also been reported among Syrian refugee women living in Lebanon, including menstrual irregularities (54%), pelvic pain (52%), and RTIs (53%) (10). The prevalence of MH problems was also found to be quite high among Syrian refugees in Lebanon, where it is estimated that 44% suffer from major depressive disorders, disproportionately affecting women (14), 38% from schizophrenia (15), and 27% from post-traumatic stress disorder (16). The high prevalence of MH problems is concerning as it interferes with the ability to make informed SRH decisions, often leading to inconsistent contraceptive use, increased risks of unwanted pregnancies, unsafe abortions and increased risk of human immunodeficiency virus (HIV) and other sexually transmitted infections (STIs) (17).

The aforementioned concerns have been equally voiced by the Ministry of Public Health (MoPH) and humanitarian agencies in Lebanon (4). The highest reported problems among Syrian refugee women include limited awareness of safe motherhood practices, symptoms of complications during pregnancy, and family planning. The main SRH stakeholders in the country agree that effective community outreach is needed to enhance early detection, timely referral, as well as responsive psychosocial support and counselling services among different Non-Governmental Organizations (NGOs) and aid agencies (4). Reported barriers to accessing the needed health services include limited availability of resources and infrastructure (18), geographical barriers, cost (19), and lack of adequate awareness and education about these issues and corresponding available services (4).

Against this backdrop, a WHO psychosocial support (PSS)—SRH integrated draft intervention package was developed to be delivered to Syrian refugee adolescent girls and young women in Lebanon. The draft intervention package consists of 8 modules focused on SRH education, psychoeducation, and enhancing skills acquisition. The draft intervention package is a low-resource/low intensity intervention, that can therefore be safely delivered by non-specialists following robust training.

This paper outlines the protocol for a Randomized Control Trial (RCT) that will be conducted in Lebanon to assess the effectiveness of the PSS-SRH draft intervention package.

## Methods

### Design

This study will employ a single-blinded community-based participatory research (CBPR) approach to assess the effectiveness of an integrated PSS-SRH intervention on Syrian adolescent girls and young women refugees (aged 15–24 years) residing in vulnerable communities in the Beqaa governorate in Lebanon. The trial consists of two arms: the experimental group (EG) who will receive the PSS-SRH intervention, and the control group (CG) who will receive the same educational material by the end of the study. The primary and secondary study outcomes will be measured at baseline (T0), end-line/post intervention (T1), and at 3-months post-intervention (T2). A comprehensive process evaluation, using a mixed-method study design, will also be conducted alongside the primary intervention outcome evaluation.

### Research aims and hypotheses

The overarching aim of this RCT is to assess the impact of a low-resource/low-intensity PSS-SRH integrated draft intervention package, augmented to existent health systems, on (1) the use of selected SRH services (specifically contraception/family planning use), and (2) the well-being of Syrian adolescent girls and young women refugees, by enhancing their self-efficacy and knowledge on said topics. This would include improving contraception/family planning use and well-being among the EG compared to the CG at 3 months-post intervention (T2).

This research study further aims to conduct a process evaluation to assess intervention fidelity and attrition during intervention implementation, as well as stakeholder satisfaction and key lessons learnt to inform global-scale up in different humanitarian settings.

### Study setting

The study will be implemented in two primary healthcare centers (PHCs) operating in the Beqaa governorate in Lebanon that will be selected based on recommendations from the Ministry of Public Health in Lebanon, department of primary healthcare. Both PHCs are required to meet the following criteria (1) originally offer SRH services to female Syrian refugees, (2) have well-kept medical records of beneficiaries, (3) able to offer indoor spaces for the implementation of the study, (4) have a large number of beneficiaries to meet the required sample size, (5) able to refer refugees with potential health problems (STIs, Mental Health, etc) to relevant health centers with adequate follow up capacity. The Beqaa governorate was selected for the purpose of the study as it hosts the highest number of registered refugees in Lebanon. The Beqaa accounts for 39% of the total registered Syrian refugee population as of January 2023 according to UNHCR, and is characterized by limited human resources and infrastructure. This allows for a comprehensive assessment of the impact of the draft intervention package on a population facing considerable challenges accessing adequate healthcare services.

### Study population

The target population of the study are Syrian adolescent girls and young women refugees (age 15–24 years) residing in Beqaa governorate in Lebanon. Participants will be included in the study if they meet the following inclusion criteria: (1) are currently married and between the ages of 15–24 years, (2) completed an average stay in Lebanon for a minimum of 6 months, (3) are willing to take part in the study as indicated by them signing an informed consent (for young women 18 years of age or older) or through a legal guardian consent form and written assent for adolescents' girls between 15 and 17, (4) have none of the exclusion criteria listed below upon screening.

Participants will be excluded from the study if they meet any of the following criteria: (1) are currently pregnant and/or lactating, (2) have reported chronic health problems interfering with the ability to follow the intervention protocol, (3) have high levels of anxiety and/or depression as well as suicidal ideations and/or attempts upon screening (based on the Hopkins 25) and/or a current diagnosis of a severe mental illness, or undergoing mental health treatment (20).

These criteria were intentionally selected to ensure delivery of the intervention to the intended target group. Particularly, enrolment will be restricted to currently married Syrian refugees because sexual health topics are considered sensitive and taboo subjects in the targeted community that would not be easily discussed with girls and young women who are not married due to cultural restrictions. Therefore, selecting this as an inclusion criterion reflects the intervention's focus on FP and SRH-related decision making among those most likely to require these services. Similarly, pregnant or lactating women and individuals with severe mental illness, may have needs or unique circumstances that may impact their ability to adequately adhere to the intervention schedule and therefore may benefit from other types of referrals or support. While it is acknowledged that these criteria may limit the generalisability of the findings, they are necessary to ensure participant safety and fidelity to the intervention.

### Sample size

Sample size calculation was based on a 20% improvement in the primary outcome (use of family planning) in the EG compared to CG at 3 months post intervention (T2). A 30% baseline prevalence of family planning use was assumed in the study population based on observed prevalence of family planning use in humanitarian settings, ranging from 7.1% (in Northern Uganda), 25% (among Afghan female refugees in Pakistan), and 34.5% (among Syrian women refugees in Lebanon) (9, 21–23). Allowing for 30% attrition, a sample size of 380 adolescent girls and young women would provide a 90% statistical power to detect a difference of 20% in family planning use at 3 months (from 30% to 50%) using a two-sided 5% significance level. This is equivalent to a relative risk of 1.67. To ensure external validity of the findings, a purposive sampling strategy will be employed, as the Syrian refugee population is not homogenous in Lebanon. Specifically purposive sampling will be used at the level of the site and community outreach, and not at the level of individual participant. Ultimately, the sample will be randomised from chosen PHCs that were selected to be part of this intervention based on specific criteria discussed in an earlier section.

### Recruitment

Recruitment will be conducted through a CBPR approach. It will be facilitated by the study stakeholders, including (1) the selected PHCs, (2) Ministry of Public Health (MoPH), (3) local women committee (LWC), and (4) community coalition (CC). LWCs are women refugees from the same target community who are facing similar, social, economic and familial hardship as the target population who have pre-existing or acquired, relationship and trust with them. This will strengthen participation, trust, and comfort of the target population in the research. The CC represents individuals perceived as trusted leaders [lay community members and representatives (community gatekeepers/directors of PHCs/reproductive health program managers, representatives from the Lebanese MoPH, NGOs, practitioners, health care providers, local Syrian refugee young women and so on)].

To preliminarily identify potentially eligible adolescent girls and young women, the research team in coordination with the selected PHCs will use the study eligibility criteria of age group and residence in Lebanon for a minimum of 6 months. The centers will then contact potentially eligible participants over the phone (if ≥18 years old) or their legal guardian(s) (if <18 years old) and invite them—using a pre-written invitation script**—**to participate in a series of health days. Health days will enable the research team to identify, select, and recruit eligible adolescent girls and young women to take part in the RCT following informed consent.

Twelve to 20 health days are estimated to take place to recruit the target sample size (380 adolescent girls and young women). During the health days, the research team will explain the aims of the event and related activities in particular, and the RCT in general and will ask the invitees that are interested in participating in the study to sign a consent form or assent/parental consent. Those who consent to participate in the health days will be offered free SRH services, including an optional routine non-invasive Ob/GYN consultation, as well as women's hygiene kits and transportation compensation. Additionally, upon signing the consent form, potentially eligible participants will fill out a screening questionnaire to determine eligibility to participate in the study. If eligible, participants will fill out the baseline outcome evaluation questionnaire. If during the Ob/GYN exam, the physician recommends lab tests to rule out selected STIs and/or other morbidities, the participant will be referred to health facilities (MOPH PHCs) that offer these tests, along with future needed follow-ups for free. If potential participants are not eligible due to high levels of anxiety or depression, or suicidality identified during screening, they will be referred to free mental health services available in the region. The recruitment process is illustrated in Figure 1.

**Figure 1 F1:**
[figure not shown]
Recruitment schematic diagram.

### Informed consent and assent

Consent forms will be inclusive of all research activities under the study. Two main types of consent forms will be administered depending on whether the participant is an adult (18 years or older) or an adolescent (aged 15–17 years). For adolescents, a written consent will be obtained from the legal guardian accompanying them in addition to written assent from the adolescent girl. To avoid undue influence, the team will first obtain assent from adolescent girls. Only if they agree to participate in the study will parental consent then be sought.

For all age groups, the field researcher will be accompanied by a member of the LWC to obtain consent and ensure that the potential participant is at ease.

To ensure respect of participants' autonomy, the team will emphasize voluntary participation and no coercion or undue influence will take place when taking consent. This includes reassuring participants that refusal or acceptance to participate would not in any way influence the benefits and services they already receive from the PHC or other organizations. Issues of confidentially and willingness to leave the research at any time, even after consent, will be highlighted as well.

Although the intervention does not inherently pose any risks of harm to participants, emotional distress may surface as a result of the topics addressed by some participants. Because this is a vulnerable population, several steps will be considered to minimise undue influence on them. This includes ensuring the presence of psychologists and midwives in each session to support with emotional distress and other challenges that may arise during the session, but also systems for referral within the PHC or to other NGOs that provide specialised care in relation to protection, health, and others. Participants will be encouraged to share their experiences with the professionals and facilitators and with their peers, and the intervention will be delivered in a manner that is scientific and that encourages learning.

### Randomization

Randomization will be conducted after baseline (T0) assessments are completed and will be stratified by site. Eligible participants will be randomly allocated to EG (intervention group) or CG with a 1:1 ratio. Randomization will be conducting using a computer-generated allocation schema, generated by the study statistician. The randomization schema will use permuted block design with sizes of 4, 6, and 8 blocks in a random mixture, so that treatment allocations are equal after each block size. The young women and adolescents will then be informed of their allocation into either the EG or CG over the telephone.

Participants in the EG will be further divided into subgroups of no more than 12 participants per group. These smaller subgroups facilitate better engagement, interaction, and personalized attention, promoting a supportive and comfortable environment for the participants.

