### Intervention

The WHO PSS-SRH draft intervention package consists of eight modules/sessions focused on SRH education, psychoeducation, and enhancing skills acquisition (specifically around: emotional regulation, communication, problem management, decision-making, and self-efficacy). It is designed to be delivered by trained community paraprofessionals (non-specialists) with at least twelve years of formal education. The draft intervention package will be administered (at the selected PHCs) once a week (for each subgroup) for a duration of 90 min over a total of 8 consecutive weeks. To create a supportive and collaborative environment for the participants in the study, each LWC member will be assigned to an EG subgroup and will attend all their sessions. The involvement of LWC members is expected to build trust and ensure a culturally sensitive approach throughout the intervention delivery. This will play a crucial role in fostering a sense of community among participants, encouraging open discussions, and facilitating the sharing of experiences and ideas. A midwife and a clinical psychologist will also attend all sessions of the intervention to support the paraprofessional when/if needed and to ensure protocol adherence as well as quality and content fidelity. Importantly, the psychologist and midwife will also support participants during the session should they feel distressed, especially when discussing sensitive topics. In such an event, the psychologist or midwife would first attend to the concerns of the participant separately, and if the need arises, they may refer them to relevant care services from professionals within the given PHC or to specialised care outside of the PHC. The intervention delivery schematic (which includes personnel, location, and days of intervention delivery) is displayed in Figure 2.

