### Analysis

A detailed statistical analysis plan will be developed upon completion of the study. The data will first be downloaded from the electronic data collection software, KoBo, and imported into a statistical analysis software.

An Intent-to-treat analysis approach will be adopted to test for significant difference of primary and secondary outcomes over time. For baseline (T0) comparability, descriptive statistics (frequency distributions, means, standard deviations, medians, IQRs) will be obtained for variables collected at baseline outcome evaluation. The Chi-square test and t-test will be used to investigate whether potentially confounding variables are balanced across the two study groups. Any potential bias due to these potential confounders will be evaluated analytically by considering them in the regression model. The internal and external study validity will be evaluated by comparing baseline characteristics of those who completed the study to those lost to follow-up, and by comparing screening characteristics of those included in the study to those eligible but not consented for inclusion in the study.

For primary outcome analysis, binary outcome of FP use (yes/no) will be evaluated between baseline (T0) and endline (T1), and between baseline and 3-month follow-up (T2). To estimate treatment effects, multivariable logistic regression models will be conducted separately for T0-T1 and T0-T2 comparisons to estimate odds ratios of FP use in the intervention group compared to the control group. All models will be adjusted for potential sociodemographic confounders. Given that each model will include one change outcome per participant, within-participant correlation as a result of repeated measures will not arise within individual models.

The primary analysis will be repeated 1- to adjust for potential confounders identified in the bivariate analysis, 2- in the compliant “per protocol” subgroup that attended 6 out of 8 (75%) weekly sessions, 3- to explore the impact of missing data with multiple imputation methods, and 4- to consider the change in FP use from intervention completion to three months.

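### The sample size and the primary logistic model ignore possible correlation among women treated in the same EG subgroup; the effect is small at an ICC of 0.02 or below and material from about 0.05

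*Protocol article*

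**What the plan says.** Under Randomization, women are allocated individually 1:1, stratified by site. Only afterwards, and only in the intervention arm, "Participants in the EG will be further divided into subgroups of no more than 12 participants per group". Under Intervention, each subgroup has one 90-minute session a week for eight consecutive weeks, and "each LWC member will be assigned to an EG subgroup and will attend all their sessions". The Contamination section describes the sessions as mainly participatory group discussion. Nothing comparable happens in the control arm.

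Under Sample size, "a sample size of 380 adolescent girls and young women would provide a 90% statistical power" for 30% versus 50% family planning use at T2, "using a two-sided 5% significance level". No ICC, group size or design effect is mentioned.

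Under Analysis, the primary model is multivariable logistic regression, fitted separately for T0-T1 and T0-T2. The only dependence it considers is repeated measurement: "within-participant correlation as a result of repeated measures will not arise within individual models". A detailed analysis plan is to follow once the study is complete.

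**The concern.** This is a partially nested design: individual randomisation, with clusters created by treatment delivery in one arm only. Women who share eight weeks of discussion, peer exchange and the same local women committee member may end up with more similar outcomes than women in different subgroups. The protocol treats that group process as part of how the intervention works, so zero correlation is not a safe default.

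The Analysis section names its model and considers correlation, but deals with one source and passes over the one that the design creates. Run as written, with a positive within-subgroup correlation, the model understates the variance of the EG estimate. Confidence intervals are then too narrow and the test rejects too often. A test that corrects for this has less power than the protocol states.

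**Working it through.** **Inputs from the protocol.** N = 380, 1:1; "Allowing for 30% attrition"; 30% versus 50%; two-sided 5%; 90% power; EG subgroups of at most 12.

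**Assumed, because the protocol gives no value.** ICC between 0.02 and 0.10; subgroups close to full; attrition spread evenly over subgroups. The two-proportion test stands in for the adjusted logistic model.

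**1. Reproduce 380.** Without continuity correction, n = (1.96·√(2·0.4·0.6) + 1.282·√(0.21 + 0.25))² / 0.20² = 124 per arm; 248/0.7 gives 355. With the continuity correction, n = 134 per arm; 268/0.7 gives 383, within 3 of the stated figure. Both formulas assume independent women, so 380 contains no allowance for clustering.

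**2. Group structure.** 190/12 = 15.8, so at least 16 subgroups. Analysed: 380 × 0.7 = 266, or 133 per arm; 133/16 = 8.3 per subgroup.

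**3. Design effect, EG only.** DE = 1 + (8.3125 − 1) × ICC. The control arm keeps DE = 1.

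**4. Planned (unadjusted) test.** The ratio of true to model-based standard error is R = √((1 + DE)/2), and the actual type I error is 2·(1 − Φ(1.96/R)). At ICC 0.05, for example, DE = 1.366, R = √1.183 = 1.088, and the type I error is 7.1%.

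**5. Test that allows for clustering.** Power = Φ((0.20 − 1.96·SE₀)/SE₁), with SE₀ = √(0.24·(1 + DE)/133) and SE₁ = √((0.21 + 0.25·DE)/133). With the continuity correction, 1/133 is subtracted from 0.20.

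| ICC | DE (EG) | R | Type I error, planned test | Power, adjusted test, no continuity correction | Power, adjusted test, with continuity correction |
|---|---|---|---|---|---|
| 0 | 1.000 | 1.000 | 5.0% | 91.9% | 89.8% |
| 0.01 | 1.073 | 1.018 | 5.4% | 90.9% | 88.7% |
| 0.02 | 1.146 | 1.036 | 5.8% | 89.9% | 87.6% |
| 0.05 | 1.366 | 1.088 | 7.1% | 86.8% | 84.1% |
| 0.10 | 1.731 | 1.169 | 9.3% | 81.5% | 78.5% |

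**6. Cross-check.** A simulation of the unadjusted analysis (3,000 trials per setting, 16 groups, beta-binomial outcomes with mean 0.30) gave type I errors of 5.8%, 7.1% and 9.7% at ICC 0.02, 0.05 and 0.10, in line with the formula.

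These power figures use normal critical values. With only about 16 clusters, a small-sample correction lowers them slightly further.

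**The case against.** **The harm depends on an unknown ICC.** This stands. A reader might infer that the standard errors are certainly too small and that 90% power is certainly missed. The documents do not support that: at ICC 0.02 the uncorrected power is still 89.9% and the type I error 5.8%. Nothing in the protocol points to 0.10 in particular.

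**Sixteen groups is a minimum.** This stands too. With 8 women enrolled per subgroup (8 × 0.7 = 5.6 analysed), uncorrected power is 90.7%, 88.7% and 85.4% at ICC 0.02, 0.05 and 0.10, and type I error 5.5%, 6.3% and 7.7%.

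**The two harms belong to different tests.** Excess type I error belongs to the planned test and lost power to the adjusted one. At ICC 0.05 the planned test still rejects about 90% of the time under 30% versus 50%. The two should not be added together.

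**The type I error needs a stated null.** If the intervention affects nobody, individual randomisation protects the comparison, because subgroups are formed only afterwards. Inflation arises when group effects exist but average to zero. That null is legitimate, but it must be named.

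**Facilitators and secondary scales.** It is tempting to say that each subgroup keeps the same paraprofessional, or that every secondary scale has wrong standard errors. The text attaches only a committee member to each subgroup and does not say how paraprofessionals are allocated (the delivery figure is not visible here). No model is named for the well-being scales, so there is no standard error to fault.

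**The analysis plan can deal with it.** This stands only in part. A subgroup term or robust standard errors would be compatible with the named model. But the protocol fixes an ordinary logistic model and an unconditional power statement, and schedules the detailed plan for after the study is complete.

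**Conclusion.** The point holds in conditional form. The protocol creates clusters in one arm, while its sample size and stated primary model assume independence. Any positive within-subgroup ICC makes the planned standard errors too small.

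The loss is minor at an ICC of 0.02 or below and becomes material from about 0.05. Over the assumed range of 0.02 to 0.10, the planned test's type I error is about 6% to 9%. The adjusted test's power is about 90% to 81%, or 88% to 78% under the formula that comes closest to 380. These figures rest on near-full subgroups, even attrition and clustering by subgroup alone. Smaller subgroups would soften them; facilitators who each lead several subgroups would make the clusters fewer and larger and could worsen them. Because the clustering is in one arm only, applying the design effect to the whole trial would overstate the loss.

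**What to change.** 1. Keep the subgroup ID in the analysis data, and the facilitator ID if facilitators lead several subgroups. Hold both with the allocation records rather than in the questionnaire, so that data collectors stay blinded.
2. Before outcome data are seen, specify for the primary outcome either a partially nested logistic model (random subgroup effect in the EG only, each control woman as her own cluster) or cluster-robust standard errors with a small-sample correction for about 16 groups. Use the same approach for the secondary scales when their model is specified.
3. In Sample size, restate the 90% power as conditional on a stated ICC range, using the same formula that gave 380. If that was the continuity-corrected one, the range is about 88% to 78% for ICC 0.02 to 0.10. Quoting 90% to 81% would mix in a formula that gives 355.

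N stays at 380. The cost is one or two ID variables and some wording, slightly wider intervals, and a slightly less favourable power statement.
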